**Fig. 2 Fig2:**
[figure not shown]
Content for the schedule of enrolment, interventions and assessments according to the SPIRIT Statement [16]

Secondary outcome measures are the effect of type of anaesthesia on quality of life and patient satisfaction. Quality of life is measured using the Short Form Health Survey-12 questionnaire (SF-12). To avoid confusion, satisfaction is also measured by a NRS-like method, using an 11-point rating scale.

Other secondary endpoints include differences in pain medication and both direct and indirect medical costs. Two different validated questionnaires, developed by the institute for Medical Technology Assessment (iMTA, Erasmus University Rotterdam, www.imta.nl) are used [18]. Complications (both surgery- and anaesthesia-related) are scored as based on the complication register of the Dutch Society for Anaesthesiologists. They are classified using the validated Clavien-Dindo classification [19]. Differences between various types of remedial surgery and specific causes of inguinodynia (primary inguinal hernia repair, primary Pfannenstiel incision, other index surgery, idiopathic inguinodynia) in relation to efficacy are also determined.

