**Fig. 3 Fig3:**
[figure not shown]
Number of unique patients analysed at SolviMáx Centre of Excellence for Chronic Abdominal Wall and Groin Pain over the years

Sample size was calculated by using a web-based calculator (www.openepi.com). Results from previous retrospective studies were used as criteria for eligibility were similar ([name], [name], [name], [name], [name], [name] – unpublished observations). Additional literature regarding anaesthesia on remedial surgery is not available. Previously demonstrated success rates were 77% in the spinal anaesthesia group and 58% in the general anaesthesia group ([name], [name], [name], [name], [name], [name] – unpublished observations). Based on these data, a sample size of 190 patients is calculated to demonstrate a potential effect of either type of anaesthesia on pain relief. This volume of patients is attained after three years as based on the number of included patients in previously performed studies (Fig. 4).

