### Randomisation

Patients will be electronically randomised by the web-based research software Research Manager (RM, Cloud 9 Health Solutions^©^). No blocked randomisation or prestratification is performed. The decision to execute a neurectomy and/or mesh removal depends on patient history, physical examination and intraoperative findings [17]. Therefore, a prestratified randomisation is not possible for type of remedial surgery. Consequently, stratification will be executed within the analysis.

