### Statistical methods

Data analysis will be performed using SPSS version 22 (SPSS Inc. ^©^) for Windows. Digital data are easily exported from RM to SPSS. The primary outcome measure is pain relief using NRS as compared to the preoperative pain levels (*t*
_0_). Pain reduction is calculated by using the following formula:$$ PAINRELIEF=\left(1-\left(\mu NRS{t}_x/\mu NRS{t}_0\right)\right)\times 100 $$

Data of the general and spinal anaesthesia group will be compared using the Student’s *t* test or the Wilcoxon signed rank test, as appropriate.

Secondary outcome measures will be compared between groups at the various postoperative follow-up points. In addition, outcomes at each evaluation time (*t*
_1–_
*t*
_5_) will be compared to preoperative data within groups. The Student’s *t* test or the Wilcoxon signed rank test will be used as appropriate. *P* values ≤ 0.05 are considered statistically significant. Intention-to-treat analysis will be applied on the primary outcome measure.

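### The arm comparison for SF-12 and pain medication does not use the preoperative value, so it is less precise than the data appear to allow (secondary endpoints only)

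*Protocol article*

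**What the plan says.** Statistical methods in the protocol article sets out two steps for secondary outcomes. The first is the arm comparison: "Secondary outcome measures will be compared between groups at the various postoperative follow-up points". The second is an addition to it: outcomes at each evaluation from 1 week to 12 months "will be compared to preoperative data within groups". For both steps the named methods are Student's t test or the signed rank test: "Wilcoxon signed rank test will be used as appropriate". The threshold is that P "values ≤ 0.05 are considered statistically significant".

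Under Outcomes, the secondary measures include quality of life by SF-12, patient satisfaction and complications. The article adds: "Other secondary endpoints include differences in pain medication and both direct and indirect medical costs".

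Two other statements bear on the point. The primary outcome, pain relief, is expressed relative to the preoperative score. Under Randomisation the article says "No blocked randomisation or prestratification is performed", and announces that stratification will be done in the analysis instead. The context is the type of remedial surgery, not the patient's own starting value.

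**The concern.** If a preoperative SF-12 score and preoperative analgesic use are recorded, they are likely to be among the better predictors of the same measures at follow-up. A comparison of follow-up values alone leaves that predictable part of the variation in the standard error. Randomisation here is neither blocked nor stratified, so no design feature limits a chance difference between the arms at baseline, and part of any such difference shows up in the follow-up contrast.

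The within-arm tests do use the baseline, but they answer another question. Patients enter because their pain is unacceptable, and both arms then have remedial surgery. Improvement from surgery and from regression to the mean is expected in both arms. A before-after p-value in one arm says nothing about the difference between spinal and general anaesthesia. At stake are the precision of the quality-of-life and analgesic comparisons and the clarity with which they are reported.

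**Working it through.** **Inputs**

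- From the article: 190 patients in total; success rates of 77% and 58% in the sample size; significance at 0.05.
- Assumed because not stated: 1:1 allocation (95 per arm), two-sided testing, 80% power, no attrition.
- Assumed because absent from the documents: rho, the correlation between the preoperative and follow-up value. The range shown is 0.3 to 0.7. Equal SDs are taken throughout.

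**1. The plan's own figure.** The article states that "a sample size of 190 patients is calculated to demonstrate a potential effect of either type of anaesthesia on pain relief". The pooled two-proportion formula without continuity correction is

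n per arm = [1.96 × √(2 × 0.675 × 0.325) + 0.842 × √(0.77 × 0.23 + 0.58 × 0.42)]² / 0.19²
= (1.298 + 0.546)² / 0.0361 = 94.2, rounded up to 95.

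That gives 190 in total, an exact match, and supports the assumptions of 80% power, two-sided 5% and equal arms. It concerns the primary outcome only. No effect size is planned for SF-12 or medication.

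**2. An illustrative difference.** With 95 per arm, the unadjusted comparison has 80% power at (1.96 + 0.842) × √(2/95) = 2.802 × 0.145 = 0.406 SD.

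**3. Effect of adjustment.** With baseline as a covariate, the variance of the arm contrast is multiplied by 1 − rho². The unadjusted interval is therefore wider by the factor 1/√(1 − rho²), the detectable difference becomes 0.406 × √(1 − rho²), and power at 0.406 SD becomes Φ(2.802/√(1 − rho²) − 1.96).

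| rho | 1 − rho² | Unadjusted CI wider by | Detectable difference, adjusted | Power at 0.406 SD, adjusted |
|---|---|---|---|---|
| 0.3 | 0.91 | 4.8% | 0.388 SD | 83.6% |
| 0.5 | 0.75 | 15.5% | 0.352 SD | 89.9% |
| 0.7 | 0.51 | 40.0% | 0.290 SD | 97.5% |

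Put another way, 190 patients analysed without adjustment carry the information of 190 × (1 − rho²), or about 173, 142 or 97 patients analysed with it.

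**4. Chance imbalance.** The difference in preoperative means has standard error √(2/95) = 0.145 SD, so its 95% range is ±1.96 × 0.145 = ±0.28 SD. Only rho times an imbalance passes into the unadjusted contrast. At the edge of the range that is 0.3 × 0.284 = 0.085 SD, 0.5 × 0.284 = 0.142 SD, or 0.7 × 0.284 = 0.199 SD. Most trials would see less.

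**The case against.** The strongest reply is that nothing here is an error. A randomised comparison of follow-up values is unbiased, its type I error over randomisation is 5%, and its standard error already allows for chance imbalance. All of that stands. A reader might infer that the planned comparison is biased, or that a baseline difference passes into it in full; neither follows.

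Second, a condensed article may leave covariates to an analysis plan that is not shown. This stands in part: such a plan could add adjustment. But the article does more than stay silent. It states the comparison and the tests, neither of which takes a covariate, and assigns the preoperative value to a different step. The stratification it announces shows that these tests are not the whole analysis, but does not cover baseline values.

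Third, the wording fixes when the arms are compared, not on what scale, so a test on change from baseline would also fit. That is possible, though not the plain reading. It would not remove the gain: change has variance 2(1 − rho) relative to the follow-up value, or 1.4, 1.0 and 0.6 at rho 0.3, 0.5 and 0.7, against 0.91, 0.75 and 0.51 with baseline as a covariate.

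Fourth, a preoperative measurement is stated outright only for pain. For SF-12 and medication it is inferred from the planned comparison with preoperative data, and the schedule figure is not shown. This limit stands.

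Finally, a reader might infer that anaesthesia type will be judged by significance in one arm and not in the other. The article never says so. The within-arm tests come on top of a direct arm comparison and may simply describe the effect of surgery. That part is a caution on interpretation only.

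**Conclusion.** The point holds as one of efficiency. On the plain reading, the article does not adjust the SF-12 and medication contrasts for baseline, although it plans to compare against preoperative data. The loss is small at rho near 0.3 and substantial at 0.7. No figure in the documents narrows that range, and the true value may be at the low end after an operation meant to change the patient's state. The 0.406 SD difference shows the scale of the loss; it should not be read as an effect the trial set out to detect, nor should the 0.28 SD imbalance be set against it directly.

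The conclusion rests on preoperative SF-12 and medication data being collected, on roughly 95 patients per arm, and on the assumed rho. It is a nearly free improvement confined to secondary endpoints. Whether a signed rank test suits independent arms is a separate question.

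**What to change.** In Statistical methods, for the SF-12 summary scores and pain medication:

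- Estimate the between-arm difference by regression of the follow-up value on randomised arm and the patient's own preoperative value. Use an ordinal or count model with the same covariate for medication if it is skewed.
- Report the adjusted difference with a 95% CI.
- Handle a missing preoperative value by simple baseline imputation, so that no patient is lost for that reason.
- State that within-arm before-after results are descriptive and are not evidence on type of anaesthesia.
- Leave outcomes without a meaningful preoperative value, such as satisfaction and complications, as unadjusted comparisons.

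Confirm first against the assessment schedule that both measures are taken before surgery. If they are, the cost is a few sentences and a few lines of SPSS code, with no added patients, visits or questionnaires.

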### Recruitment

Patients will be recruited at SolviMáx once the shared decision is taken to perform remedial surgery. During the subsequent preoperative screening, eligibility of patients for both general and spinal anaesthesia is assessed. Within 14 days of consideration, informed consent is obtained. If the patient consents, the coordinating investigator will randomise the patient as previously described. Patients are allowed to withdraw at any time point during the study.

## Discussion

General anaesthesia is still applied in the majority (60–70%) of hernia operations [20]. Spinal anaesthesia, on the other hand, is only performed in 10–20% patients undergoing inguinal hernia surgery [20], although the beneficial effects regarding postoperative pain were previously demonstrated in *primary* hernia repair [21, 22]. In addition, studies on *primary* inguinal herniorrhaphy showed that spinal anaesthesia results in shorter hospital stay, less postoperative analgesic requirements, prolonged time to first analgesic requirement, equal operation room time and equal time-to-home readiness [22–24]. Only recently, a potential beneficial effect of spinal anaesthesia on surgery for groin pain was demonstrated [15]. This is the first randomised trial comparing two routine anaesthetic modalities for remedial surgery. Results of the present trial may aid in optimising care in these patient populations.

Considering groin pain relief following remedial surgery for groin pain, spinal anaesthesia is hypothesised to be superior to general anaesthesia. The assumed beneficial effect is possibly associated with the spinal block itself diminishing transmission of nociceptive signals from the operation site toward the nervous system [21, 25]. However, as potential confounding factors are not excluded, a possible beneficial effect cannot be attributed to just one particular factor. Any potential effect should be considered as the end result of the total setting of type of anaesthesia and associated factors. These confounding factors include the intrathecal administration of anaesthetics, articaine or other drugs, patient expectations, surgical stress, patient’s state (sedated or awake) during surgery, communication with patients and various other individual psychological factors. The present study is designed to generate clinically relevant conclusions that can be directly implemented in clinical practice.

In 2004, Burney and coauthors performed a randomised trial on the effects of anaesthesia in *primary* herniorrhaphy [26]. A disappointingly low recruitment rate was observed. The authors stated that patients had conceptualised concerns regarding the anaesthetic techniques, and consequently did not accept a random assignment [26]. It is theoretically possible that patients who are more anxious about the upcoming surgical procedure prefer general over spinal anaesthesia as they do not wish to experience any ‘noise’ from within the operation room. Studies have demonstrated that anxiety is a risk factor for postoperative pain [27–29]. When these patients are prone to more intense postoperative pain and thus prefer general anaesthesia, these issues may have influenced previous outcomes. In contrast, another study showed that preferred type of anaesthesia did not contribute to success after remedial surgery ([name], [name], [name], [name], [name], [name] – unpublished observations). In SolviMáx, a standard set of intake questionnaires is obtained from all preoperative patients including a Pain Catastrophising Scale (PCS) and a Hospital Anxiety and Depression Scale (HADS) [30–32]. By analysing these scores in relation to outcome, it is possible to analyse the influence of mental status in a later phase.

The majority of studies on chronic postoperative pain lack sufficient data to draw any robust conclusions. Previously, authors have claimed that extensive preoperative data, detailed characteristics of surgical procedures and measures of acute and chronic postoperative pain (up to 1 year) are essential for a proper evaluation of effects on pain [29]. The present trial design has included all of these factors and, therefore, the results can be considered of sufficient scientific evidence. Furthermore, cost-effectiveness of both anaesthetic techniques is assessed, which is critical for clinical practice.

A potential limitation of the present study is its nonblinded design. Blinding of patients is, in our opinion, unethical and hardly practicable. Moreover, the main outcomes of the present trial are subjective. Consequently, these outcomes may be contaminated by recall bias if patients enrolled in the trial are not blinded to their treatment allocation [33].

This is the first large randomised controlled trial comparing two routinely used anaesthetic techniques in remedial surgery for groin pain. There is a definite need for evidence-based strategies to optimise the results of these types of surgery. Besides pain relief, other patient-related outcome measures are assessed to include patient’s perspectives on outcome. The first study results are expected in 2019 and will be communicated via publication.

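### The arm comparison is unadjusted although intake anxiety, which the protocol itself calls a risk factor for postoperative pain, is already collected: a modest, nearly free gain in precision is forgone

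*Protocol article*

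**What the plan says.** All references are to the protocol article.

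- **Discussion.** The text states "Studies have demonstrated that anxiety is a risk factor for postoperative pain". It reports that the clinic's standard intake questionnaires, which include HADS and the Pain Catastrophising Scale (PCS), are completed by every preoperative patient. Of their use it says "By analysing these scores in relation to outcome, it is possible to analyse the influence of mental status in a later phase".
- **Randomisation.** "No blocked randomisation or prestratification is performed". Stratifying at the analysis stage is announced, but only for type of remedial surgery.
- **Statistical methods.** "Data of the general and spinal anaesthesia group will be compared using the Student’s" *t* test, with the Wilcoxon signed rank test as the alternative. No covariate is named. The preoperative NRS enters only as the denominator of percentage pain relief.
- **Sample size.** "Previously demonstrated success rates were 77% in the spinal anaesthesia group and 58% in the general anaesthesia group". From these rates "a sample size of 190 patients is calculated to demonstrate a potential effect of either type of anaesthesia on pain relief".

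**The concern.** The protocol identifies a prognostic factor for its own outcome, measures it before surgery in every patient, and does not use it in the treatment comparison it describes. Two things are at stake.

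1. **Precision.** Any variation in pain relief that anxiety explains stays in the residual variance, so the confidence interval for the spinal–general difference is wider than it needs to be.
2. **Chance imbalance.** Simple randomisation balances anxiety only on average. If one arm happens to be more anxious, the unadjusted estimate carries that difference. A later analysis of scores against outcome, as the text describes it, is not stated to correct the arm contrast.

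The Randomisation section already accepts the principle, since it handles type of surgery in the analysis because it cannot be stratified beforehand. Type of surgery depends partly on intraoperative findings. An intake score does not, and so is the cleaner baseline covariate.

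**Working it through.** **Inputs**
- From the documents: success rates 77% and 58%, total 190 (Sample size); *P* "values ≤ 0.05 are considered statistically significant" (Statistical methods).
- Assumed because not stated: two-sided test, 1:1 allocation, 80% power.
- Assumed because the documents give nothing: correlation *r* between intake anxiety and pain relief, 0.2 to 0.4, with 0.1 and 0.5 shown as wider limits.

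**Step 1. Reproduce the plan's sample size.** The mean rate is (0.77 + 0.58)/2 = 0.675.

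n per arm = [1.96 √(2 × 0.675 × 0.325) + 0.8416 √(0.77 × 0.23 + 0.58 × 0.42)]² / 0.19²
= [1.298 + 0.546]² / 0.0361 ≈ 94.2, rounded up to 95.

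That is 190 in total, an exact match without continuity correction. Power at 95 per arm is 80.3%, so there is little reserve. This calculation is for success proportions, whereas the planned test is on percentage pain relief. The steps below therefore take 80.0% as a convenient starting power for a continuous outcome, not as a figure from the plan.

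**Step 2. Chance imbalance in a standardised score.** SE = √(1/95 + 1/95) = 0.145 SD. The 95% range is ±1.96 × 0.145 = ±0.28 SD. Unequal arms hardly matter: the SD of an arm's size is √(190 × 0.25) = 6.9, and a split of 88 to 102 gives √(1/88 + 1/102) = 0.145.

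**Step 3. Effect of an imbalance on the unadjusted estimate.** Shift = imbalance × *r*.
- At the edge of the 95% range: 0.284 × 0.2 = 0.06 to 0.284 × 0.4 = 0.11 outcome SD.
- At a typical (one-SE) imbalance: 0.145 × 0.2 = 0.03 to 0.145 × 0.4 = 0.06 outcome SD.

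**Step 4. Precision.** Adjustment multiplies residual variance by (1 − *r*²). Power = Φ(2.802/√(1 − *r*²) − 1.960), where 2.802 = 1.960 + 0.842 gives 80.0% unadjusted. Equivalent unadjusted sample size = 190/(1 − *r*²).

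| Assumed *r* | Variance removed | Power | Equivalent unadjusted N |
|---|---|---|---|
| 0 | 0% | 80.0% | 190 |
| 0.1 | 1% | 80.4% | 192 |
| 0.2 | 4% | 81.6% | 198 |
| 0.3 | 9% | 83.6% | 209 |
| 0.4 | 16% | 86.4% | 226 |
| 0.5 | 25% | 89.9% | 253 |

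If baseline NRS is also in the model, *r* must be read as the correlation that remains after NRS is accounted for, so the gain credited to anxiety alone may be smaller.

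**The case against.** **The article is condensed, and covariates are often left to the analysis plan.** This stands in part. Nothing in the text forbids adjustment, and if an analysis plan already specifies an adjusted model the point is met. But the article does not leave the comparison open: it names the test. The point concerns that stated method.

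**Randomisation already deals with anxiety.** A reader might infer from the Discussion that the trial's comparison will be confounded by anxiety. The documents do not support that. The passage concerns patients choosing their anaesthesia in earlier non-randomised data. Random allocation removes that confounding in expectation, and the standard error of the unadjusted test already allows for chance imbalance. What remains is efficiency and the imbalance in the one randomisation actually obtained.

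**The anxiety argument is tentative.** A reader might take it as the protocol's chief criticism of earlier evidence. It is offered as a theoretical possibility and followed by an unpublished study in which preferred anaesthesia did not contribute to success. The general statement that anxiety is a risk factor is not withdrawn, however, and that is all the point needs.

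**Other readings go beyond the text.** Catastrophising is measured but not called a predictor. The later analysis is described as possible, with no model given, so it cannot be said to ignore treatment arm. Nor does the protocol ask whether the spinal–general difference varies with anxiety.

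**The gain is small and unsized, and the remedy is not quite free.** This is fair. At *r* = 0.1 the gain is 0.4 power points. The scores come from routine intake and are not listed among the trial outcomes in the text, so their completeness among randomised patients is unknown.

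**Conclusion.** The point holds as a recommended improvement to a stated method. It is not an error that invalidates the comparison. A baseline factor that the protocol calls prognostic, already collected, is absent from the named arm comparison and is not balanced by design.

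Under the assumed correlation of 0.2 to 0.4, adjustment is worth about 1.6 to 6.4 power points, or the equivalent of 8 to 36 extra patients (198 − 190 to 226 − 190), less any overlap with baseline NRS. It would also remove the linear effect of a chance imbalance that, at the edge of its 95% range, could move the unadjusted estimate by about 0.06 to 0.11 outcome SD. Only the ±0.28 SD range is free of the assumed correlation; it rests on 95 per arm.

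**What to change.** In Statistical methods, prespecify the primary between-arm estimate, with its confidence interval, from a linear model for each patient's pain relief. Include treatment arm, HADS anxiety score and baseline NRS as covariates. Use only scores recorded before randomisation. PCS may be added but is optional.

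Keep patients with a missing intake score in the analysis by simple imputation from baseline data, for example the mean over both arms combined. Report the unadjusted comparison as a sensitivity analysis. An arm-by-anxiety interaction may be reported as exploratory; it is not required.

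The cost is small: no new patients or measurements, and SPSS fits the model directly. The real changes are the move from a *t* or Wilcoxon test to a linear model, and a rule for missing scores. The article gives the trial's status as recruiting, so the choice should be fixed before outcomes are compared by arm.
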